### 2. Aims

(1) To evaluate the feasibility and efficacy of EMA-based smoking cessation intervention for smoking cessation

(2) To analyze the association between smoking cues and smoking-related behaviors in the local context. Smoking cues include exposure to POS tobacco displays, health warnings, scenes of others' smoking, alcohol use, social gathering, media items on promoting smoking cessation, feeling stressed/depressed, and other smoking-related cues. Smoking-related behaviors include purchase of tobacco, tobacco consumption, and nicotine craving.

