***Pilot study*** I have conducted a pilot study (first in Asia) to examine the feasibility of using low-intensity EMA for documenting smoking cues and smoking-related behaviors (See additional materials). In total, 302 smokers installed the EMA app (designed by the primary investigator) in their own smartphone for a 2-day data collection and contributed 1,744 EMA (48% of all EMA prompts) and 693 valid EMA pairs for further analysis. The completion rate of 4+ and 6+ EMA pairs in the overall participants was 29.1% and 13.2%, respectively. Findings showed that exposure to tobacco point-of-sale (POS) displays (odds ratio [OR]=19.55,  $p<.01$ ) and health warnings (OR=14.27,  $p<0.02$ ) were significantly associated with subsequent purchase of tobacco, consistent with other EMA observational studies. Exposure to the POS displays apparently led to subsequent craving (OR=1.57) and tobacco consumption (OR=1.47), but the sample size was not sufficient to show statistical significance. Findings were presented in the International Symposium on Digital Health 2019 (20).

During Jan 2020 to Oct 2020, I conducted another pilot study using EMA to investigate exposure to alcohol advertisements and alcohol drinking culture in university students. Participants completed 5 regularly prompted EMA surveys with an EMA app in their smartphone every day for 14 consecutive days. The results showed that the 48 participants responded in 2474 EMA (73.5% of all EMA prompts). The compliance rate of 49+ (70%) and 56+ (80%) EMA was 70.8% and 45.8%, respectively.

These two pilot studies suggests several improvements to increase the EMA compliance: (1) Complicated steps to set up an EMA schedule with the EMA app increase participants' burden in real-world participation. Future app development should reduce these complicated steps and use a more user-friendly interface. A simpler set-up procedure can also save recruitment time for each participant in the outdoor environment, as their available time for recruitment is limited. (2) To sustain a higher EMA compliance for time-based system-triggered EMA, separate assessments (in the alcohol EMA pilot study) is more preferred than pair-based assessments (in the tobacco pilot

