## **11. Intervention**

***Smartphone application*** A EMA app will be developed to facilitate documentation of all smoking cues and smoking-related behaviors. After each recruitment, the staff will set up all EMA schedules of the participants in the back-end. Participants can then receive the EMA prompts and complete the EMAs. Participants will use the last 5 digits of their mobile phone numbers as identifier. They will use the app to complete an EoD survey and 4 time-based EMA each day in the 7 consecutive study days.

In each time-based EMA time window, the app will firstly prompt the user to answer questions on the smoking cues, smoking behaviours, and the association between smoking cues and smoking-related behavior, which only takes about 1 minute. If the user does not respond to an EMA prompt, 2 subsequent prompts will be generated. If these additional prompts are not responded to, the EMA will regard nonresponse as missing data. All data will be uploaded to our server immediately after each EMA completion.

The EMA questions on smoking cues cover 3 domains: mood, sleep, environmental triggers. The mood domain includes (1) irritable, depressed, restless, tension, stress, and other emotional cues related to smoking; Sleep domain includes insomnia symptoms for the last night. Environmental triggers include (1) social gathering; (2) family/friends/partner smoking; receive tobacco products/encouragement from others; (3) any other environmental smoking cues. Smoking-related behaviors include (1) nicotine craving (2) whether he/she has bought/consumed tobacco (traditional cigarettes, heated tobacco products and electronic cigarettes) in the past 3 hours (yes/no), (3) whether the tobacco consumption has been due to the exposure to the pro-smoking cues, and (4) other reasons of tobacco consumption (e.g., kill time, habit, leaving a place where smoking is not allowed). EoD survey includes (1) daily tobacco consumption; (2) time to consume the first cigarette after waking; (3) all EMA questions; (4) tobacco control policy questions which include daily exposure to health warnings on their tobacco pack/POS tobacco display/exposure to hotspot.

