#### **14. Statistical analysis**

Intention-to-treat approach will be used to include all consented participants in the analysis and assume non-respondents at the 3-month follow-up as smokers. Chi-squared and t-tests will be used to compare sociodemographic and smoking characteristics of participants to assess the balance between intervention and control group.

The primary comparison is the prevalence of tobacco abstinence and the score of IBC-S between the EMA-based smoking intervention group and the control group. Logistic regression model and linear regression will be used to compare the 7-day PPA and the score of IBC-S between intervention and control group at 3 months, respectively. We will also use multiple logistic regression and multiple linear regression adjusted for imbalance socio-demographic smoking characteristics assessed at baseline to account for imbalances in baseline characteristics.

We will transfer checklist options of smoking cues to binary outcomes. For example, an EMA question asked 'In the past 3 hours, have you been exposed to (check all that apply)' followed by these checklist options: family smoking; friends smoking; partner smoking; receive tobacco products from others; receive encourage of smoking from others). We will recode response into a series of dichotomous variables. Generalized estimating equation analysis will be used to examine the causal relationship between smoking cues and smoking-related behaviors in all participants. A linear mixed model will be used for the association analysis when the outcome is not binary.

Direct operating costs will include app development, salary (of nurses and research assistants), recruitment, telephone follow-up, and publicity items. Costs for study design, analysis, report

writing, and irrelevant administration will be excluded. The cost per successfully recruiting a smoker to participate will be calculated by dividing the total cost by the number of smokers who have joined. Similarly, cost per participant who use smoking cessation aids and per quitter at 3-month follow-up will be calculated.

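### Section 14 calls the cue–behaviour GEE causal, but the main cues and outcomes share one 3-hour recall window, policy cues are asked once a day, and no lag is stated

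*Protocol*

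**What the plan says.** - **Analysis label.** Protocol section 14: "Generalized estimating equation analysis will be used to examine the causal relationship between smoking cues and smoking-related behaviors in all participants". The following sentence uses weaker language: "A linear mixed model will be used for the association analysis when the outcome is not binary".
- **Aim.** Protocol section 2, Aim 2: "To analyze the association between smoking cues and smoking-related behaviors in the local context". POS displays and health warnings come first in its list of cues.
- **Cue window.** The example checklist question in section 14 begins "In the past 3 hours, have you been exposed to (check all that apply".
- **Outcome window.** Section 11 asks, in the same survey, "whether he/she has bought/consumed tobacco (traditional cigarettes, heated tobacco products and electronic cigarettes) in the past 3 hours (yes/no". Craving has no stated window. The sleep item refers to the previous night.
- **Policy cues.** Section 11 lists them in the end-of-day (EoD) survey only: "tobacco control policy questions which include daily exposure to health warnings on their tobacco pack/POS tobacco display/exposure to hotspot".
- **Pairing.** From its pilots, section 4 concludes that, to sustain compliance, "separate assessments (in the alcohol EMA pilot study) is more preferred than pair-based assessments". No lag between cue and behaviour is stated to take the place of the pairs.
- **Schedule.** Sections 6 and 8 give four time-based prompts and one EoD survey a day for 7 days, 3 hours apart in the worked example. The EoD survey repeats all EMA questions (section 11).

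**The concern.** Section 4 rests the causal value of EMA on measuring exposure and outcome at different times. The tobacco pilot collected EMA pairs and reported purchase that followed exposure. Read literally, the current analysis could relate a cue and an act of smoking or buying reported in the same survey over the same 3 hours. Either could have come first.

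For the policy cues the reverse direction is close to built in. Buying cigarettes in a shop exposes the smoker to the display, and smoking exposes the smoker to the pack. A single daily report cannot separate these from an effect of the display or the warning.

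There is a second route to a false result. If some people both meet more cues and smoke more often, a GEE with an uncentred cue carries that between-person difference into the cue coefficient.

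The Aim 2 evidence is at stake. Section 4 criticises cross-sectional surveys for failing to show causality and wants local evidence for measures such as display bans. A result labelled causal on this basis would be open to the same criticism.

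**Working it through.** The plan gives no sample size, power or effect figure for this analysis, so there is none to reproduce. The check has three parts.

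**1. Time order, item by item**

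| Item | Window stated | Order relative to purchase/consumption in the same report |
|---|---|---|
| Environmental cue checklist | past 3 hours | unknown |
| POS display, pack warning, hotspot | whole day, EoD only | unknown |
| Insomnia | last night | precedes daytime behaviour |
| Purchase/consumption (outcome) | past 3 hours | – |
| Craving (outcome) | none stated | cannot be judged |

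The same-window problem therefore applies to the checklist cues and the policy cues against purchase and consumption. It does not apply to insomnia and cannot be asserted for craving.

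**2. What the schedule allows**

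Inputs: 440 participants (section 7), 7 days, 4 prompts plus 1 EoD survey a day, and pilot response of 48% and 73.5% of prompts (section 4).

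- Same-day lag-1 pairs per person: (4 − 1) × 7 = 21 with time-based prompts only; (5 − 1) × 7 = 28 with the EoD survey.
- Usable pairs, assuming the two prompts of a pair are answered independently: 440 × pairs × response².
  - At 48%: 440 × 21 × 0.48² ≈ 2,130, and 440 × 28 × 0.48² ≈ 2,840.
  - At 73.5%: 440 × 21 × 0.735² ≈ 4,990, and 440 × 28 × 0.735² ≈ 6,660.
- Policy-cue reports: at most 440 × 7 = 3,080; about 1,480 at 48% and 2,260 at 73.5%, with no order within the day. Relating them to the next day leaves 7 − 1 = 6 day pairs per person.

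**3. Size of the bias when the cue has no effect**

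These are simulations with assumed parameters. They show direction and a range, and do not predict this trial.

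(a) Setting: 440 people, 7 days, 5 prompts a day, exchangeable GEE, 20 runs, true OR 1.0. The trait shifts the log-odds of both cue and smoking by 1.0 per SD. The reverse effect of smoking on the cue in the same window is a log-OR of 0.7, that is OR e^0.7 ≈ 2.0.

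| Source of bias | Same-window OR | Lagged OR | Lagged OR, person-mean-centred |
|---|---|---|---|
| None | 1.00 | 1.00 | 1.00 |
| Reverse direction only | 2.00 | 0.99 | 0.97 |
| Shared trait only | 1.10 | 1.13 | 0.99 |
| Both | 2.14 | 1.14 | 0.98 |

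The lag removes the reverse direction but not the trait. Centring removes the trait. Both are needed.

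(b) Setting: trait only, 28 prompts per person, uncentred cue, trait effect varied from 0.3 to 1.0 per SD.

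- Exchangeable working correlation: spurious OR about 1.07 to 1.14.
- Independence working correlation: spurious OR about 1.08 to 2.04.
- Person-mean-centred cue at trait effect 0.7: OR 1.00 to 1.01.

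The size depends heavily on the working correlation, which the protocol does not state.

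**The case against.** The strongest reply is that *causal* is one loose word. Aim 2 and the adjacent sentence say association, and lag, covariates, centring and working correlation are details that a statistical analysis plan normally holds. That plan is not shown. The reply stands in part: silence on centring is not an error in itself, and the protocol nowhere says that within- and between-person effects will be pooled. It does not rescue the causal claim, which is stated text, nor the once-daily policy items, which are a feature of data collection that an analysis plan cannot undo.

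A reader might infer more than the documents support:

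- *That Aim 2 itself is causal.* It is not; only section 14 uses the word.
- *That the data cannot order cue and behaviour at all.* Prompts 3 hours apart do give ordered pairs for the checklist cues, and policy cues can be related to next-day behaviour. Dropping paired prompts was a stated compliance decision and does not remove this option.
- *That confounding by traits would by itself reproduce the pilot's ORs of 1.47 and 1.57.* A spurious OR near 1.5 arises with independence working correlation and an assumed trait effect of 0.7. With exchangeable correlation it is about 1.1. The pilot ORs also concern POS displays measured in pairs, not a generic cue asked at every prompt.
- *That alcohol use and cessation media, both named in Aim 2 ("alcohol use, social gathering, media items on promoting smoking cessation, feeling stressed/depressed, and other smoking-related cues"), will not be measured.* They are not named among the section 11 items, but the list has catch-all categories and is not shown to be the full questionnaire.

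**Conclusion.** The concern holds in a limited form. Section 14 labels as causal an analysis that Aim 2 and its own next sentence call association. For the checklist cues and the policy cues, the plan as written gives no time order to support the label. Same-window reverse causation could produce an association about as large as the reverse effect itself (OR about 2.0 when 2.0 is assumed). An uncentred GEE could add a between-person component of about 1.07 to 1.14, or 1.08 to 2.04, depending on working correlation. These sizes rest on assumed trait and reverse effects that the documents do not give; only their direction is firm.

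The point concerns the observational aim alone. The randomised comparison of abstinence and IBC-S score is not touched. It deserves correction because Aim 2 is one of two stated aims and its results are meant to inform policy.

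**What to change.** 1. In section 14, replace the causal wording with association, to match Aim 2.
2. For the 3-hourly cues, make the main model behaviour at prompt t on the cue at prompt t−1 of the same day, adjusted for behaviour at t−1 and time of day. Enter each cue as the person's mean plus the deviation from it, and interpret the deviation term.
3. Label same-window results, and results for the once-daily policy cues, as descriptive same-day associations. The exception is a policy cue related to next-day behaviour.

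These changes need no new data. The cost is the loss of the first prompt of each day as an outcome and of every pair with a missed prompt. At the pilots' response rates and under independence, that leaves about 2,130 to 4,990 pairs, or 2,840 to 6,660 with the EoD survey. Lagged effects also describe the next 3 hours, so a cue that acts within minutes will be understated.

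Optional: move the POS display and pack-warning items into the 3-hourly checklist. This would give the policy cues the same time order, but it lengthens every prompt in a deliberately low-intensity design whose tobacco pilot had 48% of prompts answered. The sponsor must weigh that burden and decide before data collection, because the timing cannot be recovered afterwards.

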## **15. Consent**

Participation in the study is voluntary. The recruitment staff will first explain the project's details to the potential subjects who agree to join the study before seeking consent. The potential subjects will be assured that they can withdraw from the study anytime without any prejudice, and all the information will be kept confidential and results will be reported in an aggregate format. After that, subjects will be directed to an online form on Qualtrics to consent to participation.

## **16. Ethics**

Ethics approval will be sought from the Institutional Review Board of the University of Hong Kong / Hong Kong Hospital Authority Hong Kong West Cluster.

## **17. Direct access to source data/documents**

The EMA mobile App will only request participants to enter research data, and a 5-digit case number will be used for necessary identification. The raw data from the baseline survey, EMA App and post-EMA survey will be stored in an external hard-disk and locked in a cupboard with keys kept by the Principal Investigator. Only the investigators and research assistants of the project will be permitted to access the raw data and/ or study records. The data will be scanned and kept for 10 years or longer after the study is completed. Individual participants will not be directly identifiable from the dataset to be used for analysis.

### 18. Chronological outline of research plan

| Year                                       | 2021 |   |   |   |   |   |   |   |   |    |    |    | 2022 |   |   |   |   |   |   |   |   |    |    |    |
|--------------------------------------------|------|---|---|---|---|---|---|---|---|----|----|----|------|---|---|---|---|---|---|---|---|----|----|----|
| Month                                      | 1    | 2 | 3 | 4 | 5 | 6 | 7 | 8 | 9 | 10 | 11 | 12 | 1    | 2 | 3 | 4 | 5 | 6 | 7 | 8 | 9 | 10 | 11 | 12 |
| Development of the instrument and protocol |      |   |   |   |   |   |   |   |   |    |    |    |      |   |   |   |   |   |   |   |   |    |    |    |
| EMA App production                         |      |   |   |   |   |   |   |   |   |    |    |    |      |   |   |   |   |   |   |   |   |    |    |    |
| Subjects recruitment and data collection   |      |   |   |   |   |   |   |   |   |    |    |    |      |   |   |   |   |   |   |   |   |    |    |    |
| Data analysis                              |      |   |   |   |   |   |   |   |   |    |    |    |      |   |   |   |   |   |   |   |   |    |    |    |
| Report writing                             |      |   |   |   |   |   |   |   |   |    |    |    |      |   |   |   |   |   |   |   |   |    |    |    |

## **19. Deliverables**

The initial findings will be submitted for application for the coming round of the Health Medical Research Fund. The findings will be disseminated through publication in the journal *Addiction* or *Addictive Behaviour*.

## **20. Dissemination of study result**

The research findings will be disseminated in local and international conferences related to public health or substance use.

## **21. Financing and insurance**

Research Fund: Health Medical Research Fund Research Fellowship Scheme

